# Efficacy and safety of *Ding-Kun-Dan* for female infertility patients with predicted poor ovarian response undergoing in vitro fertilization/intracytoplasmic sperm injection: study protocol for a randomized controlled trial

**DOI:** 10.1186/s13063-018-2511-0

**Published:** 2018-02-20

**Keywords:** Traditional Chinese medicine, TCM, *Ding-Kun-Dan*, Poor ovarian reserve, Diminished ovarian reserve, Infertility, Assisted reproductive technology, IVF, ICSI

## Abstract

**Background:**

Women undergoing in vitro fertilization (IVF)/intracytoplasmic sperm injection (ICSI) who have a predicted poor ovarian response (POR) present a challenge for reproductive medicine specialists. Traditional Chinese medicine (TCM) is commonly used in China for such patients, in the belief that it will improve the ovarian response and ultimately increase pregnancy rates. However, there is a lack of high-quality evidence about the effect of TCM on improving ovarian response in such patients. The purpose of this study is to evaluate ongoing viable pregnancy rate at 12 weeks’ gestation and related indicators of ovarian response in fertile women who have a predicted poor ovarian response having immediate versus delayed IVF/ICSI after 3 months of *Ding-Kun-Dan* (DKD) pre-treatment.

**Methods/design:**

This study is a multicenter, randomized controlled, parallel-group, phase III, superiority clinical trial. Two hundred and seventy-eight eligible female infertility patients with POR will be included in the study and randomly allocated into an immediate treatment group and a DKD group in a 1:1 ratio. Both groups will receive IVF or ICSI as a standard treatment while in the DKD group, a commercially available Chinese medicine, DKD, will be administrated for 3 months before the IVF/ICSI cycle starts.

The primary outcome of the study is the ongoing pregnancy rate at 12 weeks’ gestation. The secondary outcomes include total gonadotropin dosage, duration of stimulation, estradiol (E_2_) and progesterone (P) levels on human chorionic gonadotropin (hCG) trigger day, cycle cancellation rate, number of oocytes retrieved, high-quality embryo rate, biochemical pregnancy rate, the change of serum anti-Müllerian hormone (AMH), follicle-stimulating hormone (FSH), and E_2_ levels and all side effects, safety outcomes, and any adverse events.

The protocol was approved by the Ethics Committee of the First Teaching Hospital of Tianjin university of TCM (approval no. TYLL2017[K] 004).

**Discussion:**

IVF/ICSI is increasingly used to treat couples desiring a baby. Many of these women will have poor ovarian function. In China, DKD is commonly used for these patients prior to undergoing IVF/ICSI. There is no effective treatment for poor ovarian response in Western medicine currently. It is important, therefore, to undertake this randomized control trial to determine whether DKD is effective or not.

**Trial registration:**

Chinese Clinical Trial Registry, ID: ChiCTR-IOR-17011697. Registered on 19 June 2017.

**Electronic supplementary material:**

The online version of this article (10.1186/s13063-018-2511-0) contains supplementary material, which is available to authorized users.

## Background

In order to achieve a pregnancy with in vitro fertilization (IVF)/intracytoplasmic sperm injection (ICSI), eggs must be retrieved from the woman. In order to increase the number of eggs, exogenous gonadotropins are given as part of controlled ovarian hyperstimulation (COH). The ideal ovarian response is to retrieve 10–15 eggs in order to maximize the chances of a successful pregnancy [1].

There is a worldwide trend to postpone childbearing due to socio-economic reasons, with the consequence that a number of women have a poor ovarian response (POR) prior to IVF, as the women are older. The low number of eggs collected dramatically lowers their chances of successful pregnancy in IVF/ICSI cycles [2], so much so that many IVF cycles are cancelled due to a POR [3].

Numerous treatment approaches, such as changing COH protocols [3–5], increasing gonadotropin dosage [6], using dehydroepiandrosterone (DHEA) [7–9] or other forms of androgen [10, 11], or adding growth hormone (GH) [12–14] have been tried in IVF/ICSI cycles to improve outcomes. While some show more promise than others, to date none have been shown to significantly improve pregnancy rates [15, 16].

Large numbers of reports indicate that traditional Chinese medicine (TCM) is useful for regulating hormone levels, improving implantation rates, and increasing pregnancy outcome in IVF cycles. Side effects and adverse reactions to TCM are much less frequent than with Western medicine [17]. Systematic reviews suggest that Chinese herbal medicine may be beneficial in increasing IVF/ICSI pregnancy rates [18–20]. However, the quality of the primary studies was considered poor [21].

*Ding-Kun-Dan* (DKD), as one of the most famous Chinese classic gynecological medicines, which was first used in the Qing Dynasty. It is commonly used in the treatment of irregular menstruation and infertility [22]. The components include red ginseng, cornu cervi, saffron, *Radix paeoniae alba*, *Radix rehmanniae*, *Angelica sinensis*, *Scutellaria baicalensis*, *Rhizoma cyperi*, *Rhizome chuanxiong*, motherwort fruit, *Rhizome corydalis*, among others. In TCM, DKD is used to improve renal and liver functions, nourishing the *qi* and blood, regulate menstrual function, dispel melancholy, promote blood circulation, and alleviate pain. It is useful for relieving symptoms of liver and kidney insufficiency, *qi*-blood deficiency and *qi*-blood stasis.

The purpose of this study is to evaluate ongoing viable pregnancy rate at 12 weeks’ gestation and related indicators of ovarian response in female fertile who have a predicted POR having immediate versus delayed IVF/ICSI after 3 months of DKD pre-treatment.

## Methods/design

### Study design

This study is a multicenter, randomized controlled, parallel-group, phase III, superiority study. Eligible participants will be randomly assigned to the DKD group or the control group with a 1:1 ratio. The study flow is shown in Fig. 1. The study will be conducted in four stages in the DKD group and in three stages in the control group. Participants in the DKD group will receive DKD pre-treatment for 3 months before IVF/ICSI, while in the control group, participants will receive IVF/ICSI immediately without any other intervention.

**Fig. 1 Fig1:**
[figure not shown]
Study flow chart

The protocol complies with the principles of the Declaration of Helsinki as well as Good Clinical Practice (GCP) guidelines. The Standard Protocol Items: Recommendations for Interventional Trials (SPIRIT) Checklist can be found in Additional file 1.

### Participants

#### Recruitment

Potential participants will be recruited from Tianjin Medical University General Hospital (Tianjin, China), Tianjin First Center Hospital (Tianjin, China) and The Second Hospital of Hebei Medical University (Hebei, China). The participating center must have an IVF program and be able to participate fully in the study. In China, IVF centers are regulated and typically located in level-3 (the highest level) hospitals.

Our study will be propagated via the Internet, bulletin boards, and posters in communities and hospitals, with a hotline provided for potential volunteers to call. Potential participants will be asked and talk face to face with researchers, and will be given detailed information about the study. If patients are eligible and interested in participating, they will be asked to sign an informed consent. An overview of specific measurements and time points of data collection can be found in the SPIRIT Figure (Fig. 2).

**Fig. 2 Fig2:**
[figure not shown]
Standard Protocol Items: Recommendations for Interventional Trials (SPIRIT) Figure

#### Randomization and allocation

Eligible participants will be randomly assigned to the experimental group (DKD for 3 months, then IVF/ICSI) or the control group (immediate IVF/ICSI) in a 1:1 ratio by central randomization performed by an independent statistician from Tianjin CLINDA Medical Technology Co., Ltd. Random numbers will be generated by using dynamic randomization on an online computer, which will generate a randomization schedule. Recruitment, allocation, instructions how to take DKD, and study investigations will be carried out by the study investigators. The IVF/ICSI is carried out by the treating team.

#### Sample size

The sample size calculation is based on the ongoing pregnancy rate. Studies indicated that ongoing pregnancy rate of female infertility with POR undergoing IVF/ICSI cycles was 12.5% to 15.8%, with an average of 13% [23–27]. We hypothesized that a supplementation of DKD can increase the ongoing pregnancy rate to 26%.

According to the sample size of the estimation formula [28]:$$ n\kern0.5em =\kern0.5em {\left({Z}_{\alpha }+\kern0.5em {Z}_{\beta}\right)}^2\kern0.5em \left[{P}_1\left(1-{P}_1\right)+{P}_2\left(1-{P}_2\right)\right]/{\left(\varepsilon -\delta \right)}^2, $$where *n*_1_ = *n*_2_ = *n*/(1–20%), *Z*_α_ = Z_0.05_ = 1.64, *Z*_β_ = *Z*_0.8_ = 0.84, *P*_1_is the ongoing pregnancy rate of the treatment group = 0.26, *P*_2_ is the ongoing pregnancy rate of the control group = 0.13, and *ε* is the difference of *P*_1_ and *P*_2_. Assume the superiority margin is 0 (*δ* = 0).

For 80% power to detect a difference between the experimental arm and the control arm at a one-sided 5% type I error rate, we need 112 per arm. This assumes standard sample size formulae for binary outcomes using a normal approximation [28]. To account for a 20% dropout rate, we will recruit 139 patients per arm. Considering the number of outpatients in each centre will be fluctuating during the trial; therefore, we use a dynamic randomization method to generate random numbers, and so there is no strict restriction on the number of participants in each centre.

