### Statistical analysis

Statistical analysis will be performed using SAS 9.2 software package. Intention-to-treat analysis will be applied to minimize bias due to dropouts, and reasons for which patients have dropped out will be recorded in detail and analyzed after the trial. Multiple imputation analysis will be used for missing data. Normally distributed continuous variables are reported as means and standard deviations, non-normally distributed continuous variables are reported as medians and ranges, and the count data will be described by frequency, percentage and constituent ratio. Results will be presented as point estimates and 95% confidence intervals; the level of significance will be set at 5%.

Baseline characteristics of dropout patients will be compared with those who did not. As age is a crucial factor for infertility and the effect of treatment, a simple linear model with age as a covariate will be used to analyze continuous outcomes, and a binomial generalized linear model (GLM) with age as a covariate for binary outcomes.

To compare the efficacy of DKD for female infertility with POR with the control group, the Pearson’s chi-squared test will be applied to compare frequencies between groups such as the ongoing pregnancy rate, cycle cancellation rate, high-quality embryo rate. And the *t* test will be performed to compare continuous parameters (retrieved oocyte number, gonadotropin dosage, E_2_ and P level on the hCG trigger day, etc.) between the groups. In the treatment group, the rank sum test or paired-sample *t* tests will be used to compare the indicators pre- and post treatment; for instance, basic FSH, E_2_ level, and AMH level.

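### The 80% power is for a one-sided 5% test, but the planned chi-squared test at 5% with 95% confidence intervals is two-sided and has about 70% power

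*Protocol article*

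**What the plan says.** **Sample size section.** The control rate comes from earlier studies, "with an average of 13"%, and DKD is assumed to "increase the ongoing pregnancy rate to 26"%. The section says "Assume the superiority margin is 0". It uses a normal-approximation formula with Zα = 1.64 and Zβ = 0.84. The aim is stated as "For 80% power to detect a difference between the experimental arm and the control arm", and the result is that "at a one-sided 5% type I error rate, we need 112 per arm". It adds: "To account for a 20% dropout rate, we will recruit 139 patients per arm". Randomization is "in a 1:1 ratio by central randomization", so the total is 2 × 139 = 278.

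**Statistical analysis section.** Pearson's chi-squared test is named for comparing frequencies between groups, with the ongoing pregnancy rate as the first example. The section also says: "Results will be presented as point estimates and 95% confidence intervals; the level of significance will be set at 5"%. It plans an intention-to-treat analysis with multiple imputation, and a binomial generalized linear model with age as a covariate for binary outcomes. It mentions no one-sided test, one-sided p-value or 90% interval.

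**The concern.** The chi-squared statistic squares the difference between the arms, so it rejects for a large difference in either direction. At 5% it rejects when |z| exceeds 1.96, and a 95% confidence interval that excludes zero applies the same critical value. The sample size was worked out for a critical value of 1.64. The two sections therefore describe different tests of the primary outcome.

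Two things are at stake. First, a null result would be read against 80% power when the test performed had about 70%. The chance of missing the hypothesised effect rises from 20% to about 30%. Second, some results would succeed under one section and fail under the other, and the protocol does not say which section governs. The trial is unblinded, so that choice should not be left until results are known.

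The direction of effect also matters. The DKD arm starts IVF/ICSI three months later, and the Discussion says that fertility in these patients declines over time. A worse result in the DKD arm is therefore a possibility that a one-sided test would not examine.

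**Working it through.** **Inputs (Sample size section):** P1 = 0.26, P2 = 0.13, margin 0, Zα = 1.64 (one-sided 5%), Zβ = 0.84, dropout 20%, equal allocation. The difference is 0.13. The variance sum is 0.26 × 0.74 + 0.13 × 0.87 = 0.1924 + 0.1131 = 0.3055.

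**1. Reproduce the protocol's figures.** n = (Zα + Zβ)² × 0.3055 / 0.13² = (1.64 + 0.84)² × 0.3055 / 0.0169 = 111.2, rounded up to 112. Allowing for dropout, 111.2 / 0.8 = 139.0, so 139. Both figures reproduce. Power at one-sided 5% with 112 per arm is 80.1% (unpooled variance), 79.4% (pooled variance under the null) and 80.2% (exact enumeration), in line with the stated 80%.

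**2. Power of the planned test with 112 evaluable per arm, two-sided 5%.**
- Unpooled: Φ(0.13 / √(0.3055/112) − 1.96) = Φ(2.489 − 1.96) = Φ(0.529) = 70.2%.
- Pooled null variance: the mean rate is 0.195, so the null standard error is √(2 × 0.195 × 0.805 / 112) = 0.0529. Power is Φ((0.13 − 1.96 × 0.0529) / 0.0522) = 69.2%.
- Exact binomial enumeration of the Pearson test without continuity correction: 69.9%.

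**3. No dropout at all (139 evaluable per arm).** Unpooled: Φ(0.13 / √(0.3055/139) − 1.96) = Φ(2.773 − 1.96) = 79.2%. Pooled: 78.4%. Exact: 78.9%.

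**4. Dropouts counted as not pregnant.** This is an assumption for illustration; the protocol plans multiple imputation. The rates become 0.26 × 0.8 = 0.208 and 0.13 × 0.8 = 0.104, with 139 per arm. Pooled power is 66.8%. Unpooled power is Φ(0.104 / √(0.2579/139) − 1.96) = Φ(2.414 − 1.96) = 67.5%.

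**5. Size needed for 80% power, two-sided 5%.** The protocol's formula with 1.96 in place of 1.64, and unrounded normal quantiles, gives 141.9, so 142 evaluable per arm. The pooled formula gives 145. After 20% dropout these become 142 / 0.8 = 177.5, so 178, and 145 / 0.8 = 181.25, so 182 recruited per arm.

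**6. A result on which the two sections disagree (invented counts).** Take 25/112 against 15/112 ongoing pregnancies, a difference of 0.0893. The pooled rate is 40/224 = 0.1786 and the pooled standard error is 0.0512, so z = 1.75. The one-sided p is about 0.04, a success under the Sample size section. The chi-squared p is about 0.08 and the 95% interval runs from about −1 to +19 percentage points, a failure under the Statistical analysis section.

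| Two-sided 5% test | Power |
|---|---|
| 112 evaluable per arm | 69.2–70.2% |
| 139 evaluable per arm | 78.4–79.2% |
| 139 per arm, dropouts counted as not pregnant (assumption) | 66.8–67.5% |
| Stated in the protocol | 80% |

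**The case against.** The best defence is that the only explicit statement of sidedness in the protocol is the one-sided 5% in the Sample size section. The analysis section never uses the term two-sided, its 5% level is compatible with a one-sided test, and a directional decision can be drawn from a chi-squared statistic on one degree of freedom. The 95% interval could be a general reporting convention and not the decision rule. On that reading the arithmetic is right and the power is 80%.

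Part of this stands. The arithmetic is right, and two-sidedness is inferred from the named test and the interval. But that is the normal reading of a Pearson test at 5% with 95% intervals, and nothing in the section points the other way. If one-sided was meant, the analysis section is the part that needs correcting, because a one-sided 5% decision does not correspond to a 95% two-sided interval.

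Two further objections concern the size of the shortfall. Intention-to-treat with multiple imputation keeps 139 women per arm in the analysis, but imputation does not restore the outcome information lost through dropout, and even complete data on 139 fall short of 80%. The age-adjusted model could change power, but the protocol gives no figure from which to calculate by how much, and it states no one-sided rule for that model either.

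Finally, a one-sided design is legitimate in a superiority trial if declared, and the protocol gives no estimate of harm from the delay. That is fair. The possibility of harm supports choosing a two-sided test, but the finding does not depend on it.

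**Conclusion.** The concern holds. It is a mismatch between two sections, not a calculation error. The trial is sized for a one-sided 5% test, and the analysis as written is two-sided at 5%. Under the protocol's own rates and 20% dropout, power is about 70%, roughly 10 percentage points below the stated 80%. It rises to at most 78% to 79% if nobody drops out.

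These figures assume true rates of 26% and 13%, an unadjusted chi-squared test without continuity correction, and 112 evaluable women per arm unless stated otherwise. They also take the chi-squared test and 95% interval in their usual two-sided sense. Because this concerns the decision rule and the stated power for the primary outcome, it must be corrected before results are known.

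**What to change.** State in the Statistical analysis section that the confirmatory test of ongoing pregnancy is two-sided at 5%, with a 95% confidence interval. In the Sample size section, keep the derivation as a record of how 139 per arm was reached. Replace the power statement with one that matches the test: about 70% power with 112 evaluable per arm, and about 79% if all 139 are evaluable.

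If a one-sided 5% decision is truly intended, leave the Sample size section as it is. The Statistical analysis section must then say that the primary decision uses a one-sided 5% test and report the matching 90% two-sided interval.

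Either route changes wording only and leaves enrolment at 278. The cost of the first is a less favourable stated power. If the sponsor wants 80% power with a two-sided test, enrolment would have to rise to about 178 to 182 per arm from 139. The Trial status section reports 40 participants recruited, so any of these choices could be fixed early in recruitment, counting from that report.

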#### Exclusion criteria

Patients who present with any of the following conditions will be excluded: (1) other endocrine disease or autoimmune disease, e.g., polycystic ovarian syndrome (PCOS), hyperprolactinemia, thyroid dysfunction, diabetes etc., (2) any other factors known to reduce pregnancy rates in IVF/ICSI cycles, e.g., endometriosis, intrauterine adhesions, sub-mucosal fibroids, significant uterine malformations, hydrosalpinx, etc., (3) suffering serious medical, surgical or mental illness, (4) a hereditary disease or other serious illness which would be a contraindication to pregnancy, (5) allergy to any ingredient in DKD, (6) use of hormones or TCM (contraceptive drugs, ovulation-stimulating medicine, androgens, and glucocorticoid, etc.) within 3 months prior to study entry.

#### Discontinuation criteria

Reasons for discontinuation of treatment may include, but are not limited to, the following: (1) participants become pregnant during the trial, (2) participants who have experienced some complications or serious side effects), (3) participants who do not comply with the DKD regimen, as defined by less than 80% or more than 120% of the prescribed amount; using prohibited drugs as described in the protocol, such as contraceptive drugs, ovulation-stimulating medicine, glucocorticoids etc., (4) participants who request to withdraw from the trial.

### Intervention

#### DKD group

The study will be conducted in four stages in the DKD group. After a recruitment period prior to baseline assessment and randomization, DKD (water-honeyed pill) will be given to patients in the experimental group 7 g twice daily orally from the first day of their menstrual period, for 3 months. If the participant has side effects on this dose, it is permissible to reduce the dose to 3.5 g twice daily. After that, participants will undergo their IVF/ICSI cycle. Finally, a 12-week follow-up will be included.

COH prior to IVF/ICSI will be initiated on day 3 of the menstrual cycle. All participants will receive a fixed initial daily follicle-stimulating hormone (FSH) (Gonal F, Merck Serono SA, Switzerland) dose of 300 IU subcutaneously for the first 5 days [29]. Thereafter, the daily dose will be adjusted up or down according to follicular response and serum estradiol (E_2_) level, with 450 IU as the maximum daily dose allowed. Participants will receive a gonadotropin-releasing hormone (GnRH) antagonist (Cetrorelix Ac, Merck Serono, Darmstadt, Germany, or ORGALUTRAN, Merck, Kenilworth, NJ, USA) when the dominant follicle reaches 14 mm in diameter or serum E_2_ level higher than 350 pg/ml, at a dose of 0.25 mg daily subcutaneously throughout the remainder of the stimulation period. Triggering of final follicular maturation is performed as soon as one or more follicles are ≥ 18 mm in diameter with 250 μg recombinant hCG (choriogonadotropin-α, Ovitrelle, EMD Serono, Darmstadt, Germany).

Transvaginal ultrasound-guided oocyte retrieval will take place 36 ± 2 h after triggering of final follicular maturation. Oocytes will be inseminated using conventional IVF or ICSI, according to the clinical indication. Embryo transfer will be performed on days 2–3 after oocyte retrieval and a maximum of two embryos will be transferred. Surplus embryos will be cultured until the blastocyst stage and subsequently cryopreserved, for use after trial completion.

Vaginal progesterone gel (Crinone gel, 8%, Merck Serono, Switzerland) 90 mg once daily or dydrogesterone tablet (Duphaston, Abbott, Netherlands) 10 mg twice daily orally will be used for luteal-phase support from the day after oocyte retrieval for 13–15 days. If serum hCG positive, progesterone is continued until 10–12 weeks’ gestation. If hCG is negative, or if the pregnancy fails, P support is stopped. Ultrasound will be performed at 4–6 weeks and 10–12 weeks after embryo transfer to confirm clinical and ongoing viable pregnancy, respectively.

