#### Secondary outcomes

The secondary outcomes include total gonadotropin dosage; duration of stimulation; cycle cancellation rate; E_2_ and progesterone (P) levels on the hCG trigger day; retrieved oocyte number; high-quality embryo development rate; biochemical pregnancy; as well as some specific endpoints indicative of the ovarian response, such as the change of serum AMH, FSH, E_2_ level. All side effects, safety outcomes and adverse events will also be recorded. All data will be collected using an electronic Case Report Form (eCRF) and will be supervised by an independent statistician from Tianjin CLINDA Medical Technology Co., Ltd.

The standard of high-quality embryo development rate is according to the Istanbul criteria [30] as following: Grade 1 – good rating: 10% fragmentation, stage-specific cell size, no multinucleation. Grade 2 – fair rating: 10–25% fragmentation, stage-specific cell size for majority of cells, no evidence of multinucleation. Grade 3 – poor rating: severe fragmentation (> 25%), cell size not stage specific, evidence of multinucleation.

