## Discussion

POR has been a great challenge in the field of reproductive medicine. At present, there is no single intervention generally accepted as beneficial in improving ovarian reserve greatly. A review indicated that only 10% of randomized controlled trials (RCTs) reported significant improvement in reproductive outcomes among tested interventions [2]. Therefore, other new treatment options are urgently needed to improve the poor IVF outcomes in this patient population.

On the basis of more than 3000 years of clinical practice, TCM has been making an indelible contribution to human health. In 2015, Chinese pharmacologist Youyou Tu was awarded the Nobel prize in physiology or medicine for the discovery of the new antimalarial drug artemisinin and dihydroartemisinin, which was a milestone on the road of TCM development. This inspiring event encouraged the TCM community to increasingly share the benefits of TCM with Western medicine. In order to achieve this aim, TCM will need to integrate progressively, using the concepts and methods of evidence-based medicine. Research in TCM need to be transformed and improved. DKD has been widely used in the treatment of infertility, but useful empirical research is insufficient for its popularization and application. A large proportion of TCM studies to date are not good enough to convince people of its value due to less rigorous designs, small sample size and low quality.

This study is a pragmatic RCT to assess the efficacy of DKD in infertile women with POR. The main limitation of the study is that it is not blinded and is not placebo controlled. A survey has shown that 96% of POR patients would refuse to participate in a clinical trial that might include a placebo group [9]. As patients with POR have declining (over time) fertility [31], they are unwilling to “waste” 3 months to receive placebo once they are diagnosed as having POR. Therefore, eligible participants in the control group of our study will be allocated to enter the IVF cycle without any delay.

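### The reasons given for not blinding concern participants only and do not explain why embryo grading, and to a lesser degree the 12-week scan, should be done with knowledge of arm

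*Protocol article*

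**What the plan says.** All references are to the protocol article.

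- **Blinding.** The Discussion states that "The main limitation of the study is that it is not blinded and is not placebo controlled" and makes no exception for any group of staff. The support offered is that "A survey has shown that 96% of POR patients would refuse to participate in a clinical trial that might include a placebo group", together with the remark that these women do not want to lose three months on placebo.
- **Who does what.** Under Randomization and allocation, the study investigators recruit, allocate and instruct on DKD, while "The IVF/ICSI is carried out by the treating team".
- **Embryo grading.** Under Secondary outcomes, "The standard of high-quality embryo development rate is according to the Istanbul criteria". The grades turn on degree of fragmentation, cell size and multinucleation.
- **Treatment decisions.** Under DKD group, FSH starts at a fixed "dose of 300 IU subcutaneously for the first 5 days", after which "the daily dose will be adjusted up or down according to follicular response" and estradiol, up to a stated ceiling. At transfer, "a maximum of two embryos will be transferred". The control group follows the same stimulation protocol.
- **Outcomes that depend on these steps.** "The secondary outcomes include total gonadotropin dosage; duration of stimulation; cycle cancellation rate", and high-quality embryo rate is on the same list.
- **Scans.** Under Collecting trial data, ultrasonography is done by physicians who are independent of the researchers. They are not said to be unaware of the arm. The same section has the treating team perform the antral follicle count (AFC).

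**The concern.** An open-label design does not oblige every assessor to know the arm. Placebo refusal is a reason why the women cannot be masked. It says nothing about the person grading an embryo under a microscope or reading a scan at 12 weeks. The article nonetheless describes the whole trial as unblinded and stops there.

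The outcome most exposed is high-quality embryo rate. Its grading criteria are published, but applying them calls for judgement near the boundaries between grades. A grader who knows that an embryo comes from a woman pre-treated with DKD can lean one way without intending to. The analysis compares this rate directly between groups, and it is one of the outcomes that would be read as evidence of how DKD acts. A difference caused by grading could not be told apart from a difference in embryos.

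The primary outcome is less exposed, since presence or absence of a heartbeat at 12 weeks leaves little to interpretation.

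**Working it through.** **1. Reason given against staff covered.** The Discussion offers two reasons: women would refuse a trial with a possible placebo, and women will not wait three months for one. Both are about enrolment and consent. Neither bears on laboratory staff or outcome sonographers.

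**2. Outcome by outcome: where judgement enters, and can the arm be withheld?**

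| Outcome | Where judgement enters | Can the person be kept unaware of the arm? |
|---|---|---|
| High-quality embryo rate | Visual grading | Yes; grading itself does not require knowing the arm |
| 12-week heartbeat | Little | Largely; readers are already independent of the researchers |
| Total gonadotropin dose | Adjustment after day 5 | Not reliably; treating team |
| Duration of stimulation | Limited; trigger tied to an 18 mm follicle | Not reliably; treating team |
| Cancellation | Decision to stop the cycle | Not reliably; treating team |
| Embryos transferred (affects the primary outcome) | One or two, within the maximum | Not reliably; treating team |

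**3. Why the treating team will know.** Three features of the design disclose the arm:

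- The repeat hormone tests and AFC after three months are done in the DKD group only, and the treating team does the AFC (Collecting trial data). A second count identifies a DKD participant.
- DKD is dispensed at the hospital where the women are treated (Management of intervention medication).
- The women know their arm and can mention it.

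**4. Size for embryo grading.** The article states no expected high-quality embryo rate and no grader agreement, so no shift can be calculated from it.

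**5. Size of the indirect route to the primary outcome.** The article's own sample size reproduces:

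- n = (1.64 + 0.84)² × [0.26 × 0.74 + 0.13 × 0.87] / 0.13² = 6.1504 × 0.3055 / 0.0169 = 111.18, so 112 per arm.
- 111.18 / 0.80 = 138.98, so 139 recruited per arm.

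This point does not alter either number.

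Now assume that 70% to 90% of controls reach transfer and that knowledge of arm creates a 5 to 10 point gap in cancellation. Neither range is in the article.

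- Ongoing pregnancy per transfer: 0.13 / 0.90 = 0.144 to 0.13 / 0.70 = 0.186.
- Shift in the primary outcome: 0.144 × 0.05 = 0.0072 to 0.186 × 0.10 = 0.0186, or 0.7 to 1.9 points.
- Against the assumed effect of 0.26 − 0.13 = 13 points: 0.0072 / 0.13 = 6% to 0.0186 / 0.13 = 14%.

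If DKD had no effect and open-label management moved the rate from 13% by 1 or 2 points in its favour, the chance of a false positive at one-sided 5% would be about 7.7% or 11.2% with 112 per arm, and 8.1% or 12.2% with 139 per arm (normal approximation).

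**The case against.** **The article never says that embryologists know the arm.** This is true; it follows only from the unqualified statement that the trial is not blinded. Laboratory procedure is also something a journal article may leave to the full protocol. What stands is that the article makes a positive declaration about blinding and defends it with reasons that reach participants only.

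**The limitation is disclosed.** It is, and candidly. But the disclosure explains the lack of a placebo. It does not address assessors who could be masked without one.

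**A safeguard for the scan exists.** The ultrasound physicians are independent of the researchers. Independence is not masking, but with an objective endpoint it leaves little risk.

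**A reader might infer more:** that dose adjustment, cancellation and number of embryos transferred are also open to avoidable bias, because the article already separates the investigators from the treating team and the arm therefore need not reach the IVF side. The documents do not support this. The DKD-only repeat AFC by the treating team, the dispensing of DKD at the treating hospital and the women themselves all disclose the arm. Discretion is also bounded by the fixed five-day start, the 450 IU ceiling, the 18 mm trigger and the two-embryo maximum. These outcomes carry open-label risk, but an instruction to sites would not remove it.

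**The numbers rest on assumptions.** They do. They also give cycles cancelled at discretion the average chance of pregnancy. If such cycles have poorer prospects, 0.7 to 1.9 points is too high. The embryo-number route is not quantified at all.

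**Conclusion.** The point holds for assessment, not for treatment decisions. High-quality embryo rate is exposed to an assessment bias that could be avoided at little cost, and the stated reason for not blinding does not cover it. Its size cannot be derived from the article. For the 12-week heartbeat the risk is small, and masking the reader is a sensible addition rather than a correction of a serious fault.

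Dose, duration, cancellation and number of embryos transferred should be accepted and interpreted as open-label. The shift of 0.7 to 1.9 points in ongoing pregnancy is an illustration on assumed transfer and cancellation figures. It does not show that the primary comparison is compromised. The conclusion about grading assumes that the unqualified declaration of no blinding extends to the embryology laboratory. If the full protocol already provides for masked grading, the remedy is simply to say so.

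**What to change.** - **Randomization and allocation:** state that the investigators do not disclose the arm to the embryology laboratory or to the sonographers who read the outcome scan.
- **Secondary outcomes:** state that embryos are graded without knowledge of allocation.
- **Collecting trial data:** state that the 12-week scan is read without knowledge of allocation. Keep the existing independence of the ultrasound physicians.
- **Reporting:** give the reason for each cancellation and the number of embryos transferred by arm, and describe gonadotropin dose, duration, cancellation and embryo number as open-label outcomes.

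The cost is an instruction to sites, with no added staff. Masking may be incomplete: a woman may mention DKD, and anyone who performed her repeat AFC already knows her arm. No dosing, cancellation or transfer rule changes. Trial status reports 40 of the planned 278 participants recruited, so at that stage 238 / 278 = 86% were still to be enrolled and could be covered. The date of the change should be recorded so that embryos graded before and after it can be distinguished.
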